### Focus group discussions and in-depth interviews

Focus group discussions (FGDs) will be conducted with 6 to 10 randomly selected caregivers from sampled children in each school to better understand the caregivers’ perceptions on nutrition and health. The school director and teachers will be interviewed with a semi-structured questionnaire to record characteristics of children’s health challenges, and to discuss children’s nutrition and health education in the curricula, school health activities, school water and sanitary installations and, if existing, the school feeding programmes.

### Data management and analysis

Quantitative data from stool and urine examinations, anthropometrics and Hb measurements will be entered in Microsoft Excel 2010 (Microsoft; Redmond, USA). A double data entry system will be used to ensure data quality. Data will be evaluated for discrepancies and validated after removing inconsistencies. The z-score values for height-, weight- and BMI-for-age relative to the WHO 2007 reference will be calculated using WHO AnthroPlus (WHO; Geneva, Switzerland). Statistical analyses will be carried out with Stata version 13 (StataCorp; College Station, USA). Analysis of baseline data will be conducted to describe the prevalence of malnutrition, intestinal parasitic infections, WASH conditions, KAP and basic socioeconomic characteristics. Logistic regression models will be employed to estimate associations of malnutrition, intestinal parasitic infections and anaemia with risk factors.

FGDs and in-depth interviews (IDIs) will be transcribed, translated into English by bilingual research assistants and entered as Microsoft Word documents into MAXQDA version 11 (VERBI GmbH 2012; Berlin, Germany) for data coding and analysis. Main themes will be identified and coded in order to categorise explanations and descriptions of nutritional and health related perceptions and issues.

Longitudinal analysis will be conducted to evaluate the intervention effects of the complementary interventions under study. The results from the different study arms will be compared at the end of the 1-year intervention period.

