## Methods/Design

### Goal

The overarching goal of the studies within the frame of the VgtS project in Burkina Faso and Nepal is to address the current data gap on schoolchildren (aged 8–14 years) and to assess the effects of complementary school garden, nutrition and WASH interventions on schoolchildren’s health status, as assessed by a baseline and a 1-year follow-up survey through a range of previously identified nutrition, WASH and health indicators (Table 2).

**Table 2 Tab2:** Selected indicators for the two studies in Burkina Faso and Nepal

Objective	Indicator	Methods and tools	Survey module
*Individual level of child*			
To assess schoolchildren’s nutritional status at baseline and follow-up	Nutritional status (BMIZ, HAZ, WAZ and clinical signs of malnutrition)	Digital scale, height measuring board and clinical examination	Nutritional survey (module 1)
To assess the prevalence of anaemia in schoolchildren at baseline and follow-up	Anaemia based on haemoglobin levels < 11.5 g/dl for children aged 7 to 11 years and < 12 g/dl for those aged 12 to 14 years	HemoCue Hb 201^+^	Nutritional survey (module 1)
To assess the prevalence of intestinal parasitic infections in schoolchildren at baseline and follow-up	Presence and intensity of intestinal and urinary parasitic infections	Kato-Katz and formalin-ether concentration method for stool samples and centrifugation method for urine samples	Parasitological survey (module 2)
To assess schoolchildren’s nutrition and health knowledge, attitudes and practices (KAP) at baseline and follow-up	KAP related to nutrition and health	Questionnaire survey with schoolchildren Focus group discussions with schoolchildren In-depth interviews with school directors and teachers	Children’s health KAP (module 3)
*Environmental indicators*			
To assess drinking water quality of children’s drinking water recipients at baseline and follow-up	Presence of thermotolerant coliform bacteria and faecal streptococci	Portable DelAgua field kit and RAPID E. COLI 2 AGAR (coliform bacteria, *Escherichia coli*) and Bile Esculine Azide AGAR (faecal streptococci) tests	Water quality testing (module 4)
*Household level*			
* Demographic and socioeconomic data*			
To assess basic household socio-demographic and economic characteristics at baseline and follow-up	Caregiver’s age, educational level, occupational status, assets, food security	Household questionnaire	Household questionnaire survey (module 5)

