### Collection of anthropometric indicators and measuring Hb levels

Selected schoolchildren will be subjected to anthropometric measurements according to SOPs, as described by WHO, using a digital scale and a height measuring board with a precision of 0.1 kg and 0.1 cm, respectively [48]. Individual z-score will be computed using the new WHO growth reference values for children and adolescents [49]. The nutritional status of schoolchildren will be classified as follows: a z-score within the interval of −3 standard deviation (SD) < z < −2 SD will be used to classify body-mass-index-for-age (BMIZ, thinness), height-for-age (HAZ, stunting) and weight-for-age (WAZ, wasting) as moderate undernutrition, and a z-score <−3 SD to define severe undernutrition. WAZ will only be used for children aged 8–10 years as reference data are not available beyond the age of 10 years [49]. Overweight will be classified as BMIZ >1.0 SD and obesity as BMIZ >2.0 SD [50].

The Hb level will be measured to determine anaemia prevalence. A finger-prick capillary blood sample will be taken, and Hb concentration measured using a HemoCue® 201+ testing device (HemoCue Hb 201+ System; HemoCue AB, Ängelholm, Sweden). Age-specific criteria will be used to identify anaemic children: Hb <11.5 g/dl for children aged 8–11 years and Hb <12 g/dl for children aged 12–14 years [51].

Additionally in Nepal, trained health care professionals will conduct clinical examinations for detecting clinical signs of nutritional deficiencies (e.g. dermatitis, bitot’s spot, dry and infected cornea, oedema, enlargement of liver, loss of peripheral sensation, angular stomatitis, pale conjunctiva, red inflamed tongue, swelling of the thyroid gland and bowed legs) [52].

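### The risk-factor analyses of anaemia and malnutrition are named only as logistic regression, although haemoglobin and growth z-scores are recorded on continuous scales; linear models should be added alongside.

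*Protocol article*

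**What the plan says.** **Measurement.** Under Collection of anthropometric indicators and measuring Hb levels, weight and height are taken to 0.1 kg and 0.1 cm, and haemoglobin concentration is read from a finger-prick sample. Under Data management and analysis, "The z-score values for height-, weight- and BMI-for-age relative to the WHO 2007 reference will be calculated using WHO AnthroPlus".

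**Classification.** The same measurement section then cuts these values. For growth, "a z-score within the interval of −3 standard deviation (SD) < z < −2 SD will be used to classify" moderate undernutrition, with values below −3 SD counted as severe. For haemoglobin: "Age-specific criteria will be used to identify anaemic children: Hb <11.5 g/dl for children aged 8–11 years and Hb <12 g/dl for children aged 12–14" (ages in years). WAZ is used only at ages 8–10.

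**Indicators (Goal, Table 2).** Growth is listed as "Nutritional status (BMIZ, HAZ, WAZ and clinical signs of malnutrition", that is, the z-scores themselves. Haemoglobin is listed only as the dichotomy: "Anaemia based on haemoglobin levels < 11.5 g/dl for children aged 7 to 11 years and < 12 g/dl for those aged 12 to 14" (again, ages in years). Both are set for baseline and follow-up.

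**Analysis.** For associations, "Logistic regression models will be employed to estimate associations of malnutrition, intestinal parasitic infections and anaemia with risk factors". Arm effects are in a separate paragraph: "Longitudinal analysis will be conducted to evaluate the intervention effects of the complementary interventions under study". That paragraph gives no model, link or outcome scale.

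**The concern.** Infection is binary by nature, so logistic regression fits it. Anaemia and malnutrition are different: each is a cut through a value already measured on a continuous scale. Regressing the cut version on risk factors treats a child just under the threshold like one far below it, and a child just over it like one far above. If a risk factor moves the whole distribution, that discards information, most of all when the condition is rare or nearly universal. With only 8 or 16 schools, there is little information to spare.

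The haemoglobin indicator has a second weakness. The cut-off moves from 11.5 to 12 g/dl at age 12, and the same children are measured again a year later. Some will change category because of a birthday.

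**Working it through.** **1. Reproduce the article's figure.** Inputs from Sample size, Burkina Faso: 400 children in 8 schools of 50, 25% high risk (100 v 300), average infection rate 40%, odds ratio 2, coefficient of variation 10% across schools, 5% level (taken as two-sided).

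- With odds ratio 2, the high-risk rate is p1 = 2·p0/(1 + p0). Solving 0.75·p0 + 0.25·p1 = 0.40 gives p0 = 0.358 and p1 = 0.527.
- SE under the null = √[0.40 × 0.60 × (1/300 + 1/100)] = 0.0566.
- SE under the alternative = √[0.358 × 0.642/300 + 0.527 × 0.473/100] = 0.0571.
- Power = Φ[(0.169 − 1.96 × 0.0566)/0.0571] = Φ(1.02) = 85%.

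A 5000-run simulation with the school variation included gives 84.6% (Wald logistic) and 84.3% (Mantel-Haenszel by school). The stated 85% reproduces.

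**2. Same association, outcome left continuous.** Suppose a dichotomised outcome had that 40% prevalence and came from a normal variable with a constant shift.

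- Shift d = Φ⁻¹(0.527) − Φ⁻¹(0.358) = 0.067 + 0.365 = 0.432 SD.
- Power = Φ[0.432 × √(400 × 0.25 × 0.75) − 1.96] = Φ(3.74 − 1.96) = 96%.

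Simulations with school effects (4000 runs; school-stratified score test v within-school linear regression) give about 85% v 97%. Repeat runs fall within 83–85% and 95–97%.

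**3. Extreme prevalence.** The only anaemia figure for Burkina Faso is 88%, for under-fives (Background, Table 1). Applied here purely as an illustration:

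- p0 = 0.864, p1 = 0.927, d = 0.356 SD.
- Binary: Φ[(0.063 − 1.96 × 0.0375)/0.0327] = 37%.
- Continuous: Φ(0.356 × 8.66 − 1.96) = Φ(1.12) = 87%.

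Simulation with school effects gives 39% v 86%.

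**4. Why the loss depends on prevalence.** For a small constant shift, the efficiency of the cut relative to the full scale is φ(z)²/[p(1 − p)], with z = Φ⁻¹(p).

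| Prevalence | Calculation | Efficiency |
|---|---|---|
| 40% | 0.386²/0.24 | 0.62 |
| 88% | 0.200²/0.1056 | 0.38 |

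Where power is already high the gain is small. In Nepal (640 children, odds ratio 2, under-five anaemia 46%) it is 96% v 99.8%. I give no figure for WAZ, because the article limits it to ages 8–10 and the full 400 or 640 would not apply.

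**5. The opposite assumption.** Let the effect be a 0.5 SD gain only in children below the cut, 200 v 200, no clustering. The binary test then wins: about 98% v 71% at 46% prevalence, and 85% v 13% at 16%. The direction of the comparison therefore rests on the effect being spread over the distribution.

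**6. The age-12 step.** A child with haemoglobin 11.7 g/dl at both surveys who turns 12 in between is non-anaemic at baseline (11.7 ≥ 11.5) and anaemic at follow-up (11.7 < 12).

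**The case against.** The case against is substantial.

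- **Anaemia prevalence is a stated objective.** The article sets out to measure it and to fill a data gap for policy. Mean haemoglobin is a different estimand. This stands, and it is why prevalence must stay and the linear models come beside it.
- **The arm comparison is not fixed as binary.** A reader might infer that intervention effects on haemoglobin and growth will be tested by logistic regression. The article does not say so. The logistic sentence directly follows the one on baseline analysis and concerns risk factors, while the longitudinal paragraph names no model or scale. An article may leave that to the full protocol or analysis plan, so no power loss for the arm contrast can be charged to it.
- **Growth z-scores are not confined to a dichotomy.** Table 2 lists them as indicators. For growth, the point is limited to the risk-factor models, where malnutrition is the named outcome.
- **The size is not a property of the plan.** A reader might want one headline loss. The article gives no prevalence for ages 8–14 and no effect size for haemoglobin or z-scores, and step 5 shows that even the sign can change.
- **The age-specific cut-off is a cited criterion.** Children cross age 12 in every randomised arm, so the step adds noise and not bias.

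What remains is that the article does name a model and does name cut outcomes for the risk-factor analyses. That is a stated choice and can be improved on, rather than a detail left out.

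**Conclusion.** The point holds for the risk-factor associations and for the Table 2 definition of the haemoglobin indicator. Under a constant shift in a normal outcome, with the article's Burkina Faso inputs, the binary analysis has about 85% power where the continuous one has about 97% (40% prevalence). If the under-five anaemia figure carried over to ages 8–14, which the article does not claim, it would be about 39% against 86%. Both pairs are illustrations. If effects are confined to children below the cut-off, the loss could be smaller or turn into a gain for the binary analysis.

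The sample sizes and the primary outcome, intestinal parasitic infection, are untouched. This is a worthwhile improvement to secondary analyses, not a threat to the trial's main result.

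**What to change.** - **Data management and analysis, risk factors:** keep the logistic models. Add linear mixed models with a random intercept for school for haemoglobin in g/dl (adjusted for age and sex), HAZ and BMIZ, and for WAZ at ages 8–10 only.
- **Table 2:** restate the haemoglobin indicator as haemoglobin concentration and anaemia prevalence. Keep anaemia and undernutrition prevalence, by the cited cut-offs, as stated objectives.
- **Longitudinal analysis:** state that haemoglobin and the z-scores are carried as continuous outcomes adjusted for the child's own baseline value, which is already collected. For haemoglobin, this also removes the category changes caused only by turning 12.

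**Cost:** a few lines of text and some extra Stata models, with no new data or children. The downside is that a mean difference in g/dl or z-score is less familiar to policy readers than a prevalence, which is a further reason to report both.

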### Data storage and handling

All data files will be stored in a secure server at Swiss TPH. ID codes and name-linked information on participants will remain confidential and will be used only to communicate clinical results to participants for their respective treatments.

### Ethical considerations

The two research protocols for Burkina Faso and Nepal were reviewed by (i) the Institutional Research Commission of Swiss TPH (reference number FK 116; date of approval 30 October 2014); (ii) the “Ethikkommission Nordwest- und Zentralschweiz” (EKNZ) in Switzerland for the Nepal study protocol (reference no. UBE-15/02; date of approval 12 January 2015); (iii) the EKNZ in Switzerland for the Burkina Faso study protocol (reference no. 2014–161; date of approval 19 January 2015); (iv) the “Comité d’Ethique pour la Recherche en Santé, Ministère de la Recherche Scientifique et de l’Innovation, et Ministère de la Santé” in Burkina Faso (reference no. 2014-5-058; date of approval 20 May 2014); (v) the “Institutional Review Committee of Kathmandu University School of Medical Sciences, Dhulikhel Hospital”, Nepal (reference no. 86/14; date of approval 24 August 2014); and the (vi) Institutional Review Committee, Health Research Council, Nepal (reference no. 565; date of approval 11 November 2014).

The two studies have been registered under a single trial registration number at the International Standard Randomised Controlled Trial Number Register ISRCTN30840 (date assigned: 17 July 2015; http://www.isrctn.com/ISRCTN17968589).

## Discussion

Malnutrition and intestinal parasitic infections are a major burden on children’s health globally and particularly in LMIC, including Burkina Faso and Nepal. Inadequate WASH conditions play an important role in the high burden of communicable diseases [21, 57]. The morbidity due to malnutrition, intestinal parasitic infections and diarrhoeal diseases in Burkina Faso and Nepal continue to be considerable [4]. Given the global persistence of malnutrition and ill-health, the research and international development communities are increasingly paying attention to enhancing nutrition and health as the primary goals and outcomes of food production and delivery systems [58–60]. Agriculture as a source of nutritious food and well-being has recently been recognised and is addressed in the new Sustainable Development Goals (SDGs), particularly in SDG 2: “End hunger, achieve food security and improved nutrition and promote sustainable agriculture” [61]. There is, however, an insufficient evidence-base which supports these agriculture, nutrition and health linkages [58–60]. Indeed, according to Masset et al. (2011), who undertook to date the largest systematic review on agricultural intervention to improve the nutritional status of children, there is “no evidence of the impact [of agricultural interventions] on prevalence rates of stunting, wasting and underweight among children under five” [62]. Even though agriculture interventions were beneficial in promoting consumption of nutritious foods, evidence of improved nutritional indicators was not consistent [62–64]. However, according to Webb (2013), the lack of evidence on the impact of agricultural interventions on nutrition and health outcomes should not be attributed to the inefficacy of these interventions, but rather to insufficient statistical power (small simple size), lack of rigorous counterfactual analysis, inadequate selection of outcome indicators for the kind of interventions considered, and few accounted for the heterogeneity of impacts even when they were positive [60, 62, 64, 65]. Furthermore, school-aged children are moving into the focus of recent initiatives by governments, bilateral and multilateral organisations, and other development actors; which have recognised the benefits of good health and nutrition of schoolchildren to contribute to educational achievement, growth and development [3, 66–70].

The two studies in Burkina Faso and Nepal within the frame of the overall VgtS project that we describe here will support the reinforcement of this recent attention on schoolchildren’s nutrition and health by focusing on schools as an entry point for health promotion, infection control and life-skills education. Moreover, the studies will contribute to fill existing data gaps on schoolchildren in these two countries, concurrently identifying their nutritional and health challenges and needs. The data collected will serve to inform the design of appropriate and tailored school-based interventions with close participation of the local community, school teachers and directors, as well as with the local research and VgtS project team. The precise set of interventions will be developed after the baseline survey in Burkina Faso and Nepal. The interventions will be designed with a multidisciplinary team of educators, epidemiologist, nutritionist, parasitologists and WASH experts in order to improve water quality, sanitary and hygiene environments and to translate the nutritional and health risk factors into effective educational messages, thereby encouraging schoolchildren to change their behaviour.

The two studies also aim to address the scientific research gap by conducting rigorous intervention studies and quantifying the possible effects of complementary school garden, nutrition and WASH interventions. With the two particular study designs as suggested in Burkina Faso and Nepal, we will be able to analyse the different types of school garden, nutrition and WASH intervention packages. While in Burkina Faso the focus will be on the comparison of integrated and complementary school garden, nutrition and WASH interventions (arm A) as compared to the control schools with no interventions (arm B); in Nepal, we will additionally be able to conduct comparisons between these two study arms to the school garden intervention schools (arm C) and the nutrition and WASH intervention schools (arm D).

Several considerations underscore the relevance for the two concerted and complementary study designs. First, with the same research methods and questionnaire tools applied, data collected from Burkina Faso and Nepal will be used for comparative analysis. Second, the two similar study designs will offer strategies for comparing different public health approaches with an emphasis on schoolchildren’s health and will provide opportunities for discussing the long-term sustainability of these programmes, especially in areas where the targeted diseases are highly prevalent.

Taken together, the overarching goal of the two studies is to assess the potential of suitable interventions to improve health of school-aged children in resource-constrained settings. The insights gained will contribute to estimate the burden of malnutrition and intestinal parasitic infections in schoolchildren and may provide guidance for future research activities, for the implementation of health policies at the school level, as well as for future public health recommendations and health policy planning.

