### Data collection procedures

Four weeks prior to the study, district and village authorities, school directors and children’s parents/guardians will be informed about the forthcoming survey activities by the local survey team. They will be re-informed about the purpose and procedures of the study shortly before the start of the survey activities. Written informed consent (signed or fingerprint) will be obtained from children’s parents or legal guardians, whilst children will assent orally. It will be emphasised that participation is voluntary and that children and parents/guardians can withdraw anytime without further obligation.

In each school, a random selection of children aged 8–14 years will be enrolled until at least 55 in Burkina Faso and 44 in Nepal are reached. Moreover, at the follow-up survey, the same children will be re-assessed, who by then will be 9–15 years old. Each child will be attributed a unique identification code (ID) for the different assessments at the onset of the study. A separate household ID connected to the schoolchild’s personal ID will be given to children’s households in order to link children’s clinical data and nutritional and health knowledge, attitudes and practices (KAP) with the household characteristics. Children will thereafter be invited to provide stool and urine samples, to take anthropometric and haemoglobin (Hb) measurements and to participate in the KAP survey. In Burkina Faso, stool and urine samples will be collected on two consecutive days. In Nepal, a single stool sample will be collected, while urine samples will not be collected as urogenital schistosomiasis is not endemic. Infected, anaemic or undernourished children in all schools will be subjected to clinical, parasitological and nutritional examinations, and will be treated according to national policies.

After these assessments with children at the schools, the same enumerators in Burkina Faso will visit children’s households and will invite children’s caregivers to respond to a household questionnaire during the two survey days. In Nepal, due to the scattered locations and geographical constraints, additional enumerators will visit the children’s households during the same survey period. In both countries, trained and experienced enumerators will conduct the questionnaire surveys in local languages.

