### Collection of stool and urine samples

The sampled children at the schools will be asked to provide a fresh mid-morning, post-exercise stool sample. The stool samples will be processed and analysed each day (at mid-day the latest) by experienced laboratory technicians and medical microbiologists as follows: first, stool samples will be visually examined for macroscopic appearance of adult worms, also checking the stool consistency and the presence of blood and mucus. Second, a single Kato-Katz thick smear, using 41.7 mg templates, will be prepared on a slide and examined under a microscope for the presence of eggs of *Schistosoma mansoni*, hookworm, *Ascaris lumbricoides, Trichuris trichiura* and *Hymenolepis nana*, adhering to standard operating procedures [35, 36].

Third, a formalin-ether concentration technique will be used to enhance sensitivity for the diagnosis of helminths and to detect intestinal protozoa (*Blastocystis hominis*, *Chilomastix mesnili*, *Endolimax nana*, *Entamoeba coli*, *Entamoeba histolytica*/*Entamoeba dispar*, *Entamoeba hartmanni*, *Giardia intestinalis* and *Iodamoeba bütschlii*) [37]. Approximately 1–2 g of stool will be placed in 15 ml Falcon tubes filled with 10 ml of 5 % formalin and will be examined by experienced laboratory technicians for the presence of helminths and intestinal protozoa, using an ether-concentration technique, adhering to an SOP [38]. Additionally, in Nepal, 20 mg of stool will be prepared on a single slide with the saline wet mount concentration for the microscopic detection of the same intestinal protozoa and helminths, according to SOPs [39, 40]. Furthermore, the intensity of infection will be calculated as the number of eggs per 1 g of stool (EPG) and categorised according to the WHO standard classification [41].

In Burkina Faso, children will also be asked to provide fresh, mid-morning and post-exercise urine samples, collected at the same time as the stool samples. Urine samples will be analysed for microhaematuria (biochemical marker and proxy for *Schistosoma haematobium*), using reagent strips (Hemastix; Siemens Healthcare Diagnostics GmbH; Eschborn, Germany) [42], and for the presence and number of *S. haematobium* eggs in 10 ml of urine using a urine centrifugation technique and microscopy [43]. *S. haematobium* infection will be grouped into light (< 50 eggs/10 ml of urine) and heavy (≥ 50 eggs/10 ml of urine) [44].

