In order to achieve a higher sensitivity in diagnostics, in selected schoolchildren stool and urine samples will be obtained on two consecutive days in Burkina Faso [45, 46]. For quality control, 10 % of all processed stool samples will be re-read under a microscope by independent laboratories [47]. Slides identified with discrepant results will be re-examined by the Institut de Recherches en Sciences de la Santé (IRSS) laboratory and Kirnetar Health Centre team until agreement has been reached.

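### The planned Burkina Faso–Nepal comparison is justified by identical methods, but stool sampling and tests differ by country, so compared intestinal infection prevalence would mix true differences with differences in detection.

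*Protocol article*

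**What the plan says.** The Discussion gives the ground for comparing the two countries: "with the same research methods and questionnaire tools applied, data collected from Burkina Faso and Nepal will be used for comparative analysis".

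The Methods describe the following stool work.

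- **Burkina Faso, number of samples.** Data collection procedures: "In Burkina Faso, stool and urine samples will be collected on two consecutive days". Collection of stool and urine samples gives the reason and adds a restriction: "In order to achieve a higher sensitivity in diagnostics, in selected schoolchildren stool and urine samples will be obtained on two consecutive days in Burkina".
- **Nepal, number of samples.** Data collection procedures: "In Nepal, a single stool sample will be collected, while urine samples will not be collected as urogenital schistosomiasis is not endemic".
- **Nepal, extra test.** Collection of stool and urine samples: "Additionally, in Nepal, 20 mg of stool will be prepared on a single slide with the saline wet mount concentration". It is read for the same protozoa and helminths as the other stool tests.
- **Both countries.** The same section describes two tests without naming a country: "a single Kato-Katz thick smear, using 41.7 mg templates, will be prepared on a slide", and "a formalin-ether concentration technique will be used to enhance sensitivity for the diagnosis of helminths and to detect intestinal protozoa".

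Under Sample size, prevalence of intestinal parasitic infection is the primary outcome in both countries, with planning rates of 40% in Burkina Faso and 30% in Nepal. Nothing in the article limits the country comparison to the shared tests or to the first-day sample. The section on study sites does call the two designs slightly different, but that remark concerns school sampling and arms, not diagnostics.

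**The concern.** Apparent prevalence is true prevalence multiplied by the sensitivity of the whole testing procedure, if specificity is perfect. When two countries use different procedures, a difference in apparent prevalence can arise with no difference in infection. The protocol itself says that the second day raises sensitivity, so no outside source is needed to see that the procedures differ in this respect.

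At stake is any statement that one country's schoolchildren carry more intestinal infection than the other's, and any pooled model in which country or a country-linked factor is an explanatory variable. A reader of the Discussion would take such a contrast as like with like.

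**Working it through.** **1. The plan's own figures.** The article gives no figure for the between-country comparison. The nearest are the sample sizes, which reproduce. For Burkina Faso, 300 low-risk against 100 high-risk children at an odds ratio of 2 and two-sided 5% give 84.7% power if 40% is the overall rate and 85.0% if it is the low-risk rate (stated: 85%). Recruitment is 400 × 1.1 = 440 and 640 × 1.1 = 704, in total 1144. These figures are not in dispute. The useful yardstick is the gap between the planning rates: 40% − 30% = 10 points.

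**2. Procedures side by side.**

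| | Burkina Faso | Nepal |
|---|---|---|
| Stool samples | two consecutive days (all or selected children: unclear) | one |
| Kato-Katz, single smear | yes | yes |
| Formalin-ether concentration | yes | yes |
| Saline wet mount | not described | yes |

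The second day raises detection in Burkina Faso and the wet mount raises it in Nepal. The two effects oppose each other.

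**3. Size of the second-day effect alone.** Assumptions, none of them from the documents: true prevalence P equal in both countries; one sample detects a true infection with sensitivity s; days independent; perfect specificity; every Burkina Faso child gives two samples; the wet mount adds nothing.

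- Nepal reads P × s.
- Burkina Faso reads P × [1 − (1 − s)²].
- The ratio is 2 − s and the difference is P × s × (1 − s).

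| P | s | Burkina Faso | Nepal | Artefact (points) |
|---|---|---|---|---|
| 40% | 0.5 | 30.0% | 20.0% | 10.0 |
| 40% | 0.7 | 36.4% | 28.0% | 8.4 |
| 40% | 0.9 | 39.6% | 36.0% | 3.6 |
| 30% | 0.5 | 22.5% | 15.0% | 7.5 |
| 30% | 0.7 | 27.3% | 21.0% | 6.3 |
| 30% | 0.9 | 29.7% | 27.0% | 2.7 |

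**4. Would it pass for a real difference?** Take 400 children in 8 schools against 640 in 16, with the planned between-school coefficient of variation of 10%. The variance of the difference is p₁(1 − p₁)/400 + p₂(1 − p₂)/640 + (0.1p₁)²/8 + (0.1p₂)²/16. At P = 40%, s = 0.7 this is 0.00111, the standard error is 0.0333, and z = 0.084/0.0333 = 2.52. At P = 30%, s = 0.7, z is 2.13. At s = 0.9, z is about 1.0 or less. Under these assumptions the artefact alone would be expected to cross 1.96 at s = 0.5 to 0.7, but not at 0.8 or 0.9.

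**5. Relaxing the assumptions, at P = 40%, s = 0.7.**

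- The wet mount finds half of the infections otherwise missed in Nepal: 0.40 × (0.7 + 0.3 × 0.5) = 34.0%. The gap is 36.4 − 34.0 = 2.4 points.
- In addition, only half of the Burkina Faso children give a second sample: 0.40 × (0.5 × 0.91 + 0.5 × 0.7) = 32.2%, now 1.8 points below Nepal.
- If detection on the two days is positively correlated within a child, the second day adds less and the artefact in step 3 shrinks.

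**The case against.** The strongest reply is that the comparison is barely specified. One sentence in the Discussion announces a comparative analysis and names no outcome, estimand or pooled model. The objectives and the section on data management and analysis plan no between-country prevalence test, the sample sizes were calculated separately, and the arm comparisons lie within each country. The infection definition for such an analysis could be left to an analysis plan. The two core stool tests are shared, and the differences are openly described in the Methods.

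Part of this stands: no pooled model is actually planned, and the point should not be read as saying that one is. But the article does more than leave a detail open. It states a premise that its own Methods contradict and rests an analysis on it. Prevalence of intestinal infection is the primary outcome in both countries, so it is fair to expect it among the compared data.

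Several stronger readings are tempting and not supported.

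- **Burkina Faso prevalence will be overstated relative to Nepal.** Not established: the wet mount works the other way, and step 5 shows a reversal.
- **The 3 to 10 points are an estimate.** They illustrate assumed values only.
- **Urine testing adds to the bias.** Urine is examined for *S. haematobium*, which is not part of the intestinal outcome, and the protocol justifies its omission in Nepal by non-endemicity. It would matter only if the combined intestinal and urinary indicator in Table 2 were compared.
- **Water testing differs in the same way.** The drinking water section describes the *E. coli* and streptococci agars only for Burkina Faso, but Table 2 lists them for both studies. That is a mismatch to reconcile, not proof of different tests. Sampling a random 20% of households against all of them affects precision and does not by itself bias contamination prevalence.

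**Conclusion.** The point holds for the stool diagnostics. The Discussion's claim of identical methods is not true of the laboratory work behind the primary outcome, and a between-country or pooled comparison on the full test sets would confound infection with detection. The net direction is unknown. The second-day effect alone is worth about 3 to 10 points under the assumptions in step 3, at most equal to the 10-point gap between the planning rates. It shrinks or reverses once the wet mount or partial resampling is allowed for.

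A reader might infer that the trial's effect estimates are compromised. They are not: within a country the same procedures are described for every arm, so the randomised comparisons are unaffected. Anthropometry, haemoglobin and questionnaire comparisons do not depend on the stool tests.

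A related inconsistency needs settling. Data collection procedures gives two-day sampling in Burkina Faso without restriction, while the laboratory section limits it to selected children. The article also uses the word selected for enrolled children in the anthropometry section, so it may mean no more than that. If it means a subset, sensitivity also varies within Burkina Faso, which strengthens the case for a first-day definition.

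**What to change.** 1. For any cross-country or pooled analysis of intestinal infection, define infection from the first-day stool only, by one Kato-Katz smear plus formalin-ether concentration. Exclude the second-day sample, the wet mount and urine results. Keep each country's full diagnostic set for its own arm comparisons.
2. Qualify the sentence in the Discussion: questionnaires and core stool tests are shared, while the number of stool samples and the additional tests differ by country.
3. Reconcile Data collection procedures with Collection of stool and urine samples on whether all or only some Burkina Faso children are sampled on two days.
4. If water quality is to be compared between countries, first reconcile Table 2 with the drinking water section on which agars are used where. Restricting the comparison to thermotolerant coliform counts is not a sufficient repair: Nepal samples that pass the chlorine and turbidity screen are not tested for coliforms, and no such screen is described for Burkina Faso. Leaving those samples out would set all Burkina Faso samples against only the Nepal samples that failed the screen, so the plan must say how they are counted.

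The cost is small. Results must be stored by day and by method, and one derived variable is needed. No extra sampling is required. The price is lower sensitivity in the cross-country analysis only.
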